## Abstract

**Abstract:**

**Introduction:**

Chronic kidney disease (CKD) affects 1 in 10 people worldwide and can progress towards kidney failure, which is best predicted by the severity of kidney fibrosis. Currently, kidney fibrosis can only be detected by invasive kidney biopsy which carries procedural risks with limitations on repeat testing. MRI techniques have emerged as potential surrogate markers for kidney fibrosis, though data remain limited. To date, no studies have examined postgadolinium contrast T1 mapping in kidney fibrosis despite its proven utility in assessing myocardial fibrosis. This study aims to develop a multiparametric MRI biomarker including postcontrast imaging to quantify kidney fibrosis in individuals with CKD.

**Methods and analysis:**

In this observational cohort study, a control group of 20 healthy adult volunteers will establish healthy kidney MRI parameters. Two adult non-dialysis CKD cohorts (each n=24) who have undergone kidney biopsy within the last month will derive and validate the MRI models, respectively. Tubulointerstitial fibrosis on kidney biopsy will be assessed by Masson trichrome staining and quantified based on the percentage of cortex affected by blinded pathologists. All participants will undergo a single multiparametric kidney MRI including kidney volumetry, T1 mapping (pre-low-dose and post-low-dose contrast), T2 mapping, T2* mapping, diffusion weighted imaging and phase-contrast MRI of renal artery flow. The primary outcome will be the association between a composite multiparametric MRI marker and tubulointerstitial fibrosis with a minimum variance of 50%. The association between the multiparametric MRI marker and individual MRI variables, and tubulointerstitial fibrosis, estimated glomerular filtration rate and albuminuria will also be studied.

**Ethics and dissemination:**

Ethics approval has been obtained by the Northern Sydney Local Health District Human Research Ethics Committee (2022/ETH00972). Results will be disseminated in relevant peer-reviewed journals and presented at academic conferences.

**Trial registration number:**

ACTRN12622000855729p (Pre-results).

Strengths and limitations of this studyKidney MRI is a growing area of interest due to its potential to provide a comprehensive assessment of kidney microstructure, haemodynamic properties and function.This study combines emerging and novel MRI techniques to develop a non-invasive biomarker for kidney fibrosis which can currently only be quantified histologically by kidney biopsy.The multiparametric MRI models used in this study facilitate the examination of multiple MRI techniques including volumetry, T1 mapping, T2 mapping, T2* mapping, diffusion weighted imaging and phase-contrast MRI in a single examination.Limitations of this study include its limited sample size and lack of prospective follow-up, thus restricting its ability to report on the prognostic value of the proposed MRI biomarker.

## Background

 Chronic kidney disease (CKD) has a global prevalence of 13%, which is predicted to rise further.^1^ It is an independent risk factor for morbidity and cardiovascular disease and is a leading cause of non-communicable death worldwide.^2^ As such, CKD has recently been recognised as a priority within the WHO non-communicable diseases agenda.^3^ Kidney fibrosis is the strongest predictor and final hallmark of CKD regardless of underlying aetiology.^4^ Early detection and targeted therapy are essential for preventing kidney failure, yet routine clinical markers such as estimated glomerular filtration rate (eGFR) and proteinuria correlate poorly with kidney fibrosis, particularly in early disease.^5^ Currently, the quantification of kidney fibrosis relies on invasive kidney biopsy, which is often performed at advanced stages when irreversible damage has already occurred. Biopsy carries risks with a high incidence of postbiopsy perinephric haematoma and pain,^6^ making repeated procedures unsafe and preventing longitudinal monitoring of fibrosis. Further limitations of kidney biopsy include technical challenges based on patient anatomy and sampling error. Thus, there is a critical need for an alternative non-invasive biomarker to allow for the timely detection and monitoring of kidney fibrosis and identification of individuals at risk of kidney disease progression.

To this end, imaging modalities have emerged as promising tools in the assessment of CKD. In particular, there have been recent advancements in MRI techniques to assess renal function, microstructure, blood flow, perfusion and oxygenation,^7^,^10^ which offer potential for earlier detection of CKD even before clinical manifestations appear. For example, total kidney volume measured from T1-weighted or T2-weighted structural MRI is a validated biomarker in the assessment of kidney function, prognostication and treatment response in autosomal polycystic kidney disease, and has been shown to be associated with kidney function in the general population and other CKD aetiologies.^7 11^ Techniques such as T1 and T2 mapping produce maps over the kidney to quantify tissue-specific T1 and T2 values, respectively, which reflect changes in the molecular environment.^7^ T1 values are sensitive to water content, fibrosis and inflammation, whereas T2 values are more so affected by oedema and inflammation,^6^ and there are a number of ongoing studies to assess their clinical applicability in CKD and kidney transplantation.^12^ T2* mapping uses the paramagnetic properties of deoxygenated haemoglobin to indirectly assess tissue oxygenation^13^ and has been demonstrated to predict the risk of kidney function decline and kidney replacement therapy requirements in CKD.^14^ Diffusion-weighted imaging (DWI) detects the displacement of water molecules in tissue, thus potentially aiding the assessment of fibrosis, perfusion, cellular infiltration and oedema in the kidney.^15^ Phase-contrast (PC) MRI offers a non-invasive method to measure renal blood flow, enabling the assessment of renal haemodynamics in which changes occur at the earliest stages of kidney disease.^16^

A number of these MRI techniques have also been shown to correlate with histologically proven kidney fibrosis, with the most robust data being available for T1 mapping,^17^,^19^ blood oxygen level dependent imaging derived from T2* mapping^20 21^ and DWI.^17^,^2022 23^ However, these findings have been inconsistent with limited sensitivity and specificity and are yet to be validated for clinical application, highlighting the need for further studies and development.^9 24^ Multiparametric renal MRI protocols use multiple MRI techniques from a single examination to provide a comprehensive assessment of renal microstructure and function.^25^ They are proposed to enhance the detection of kidney pathology and have been recommended to be applied in future studies rather than standalone techniques.^7^ Indeed, multiparametric MRI models have been shown to provide greater accuracy in predicting kidney fibrosis compared with single MRI measures.^18^

Importantly, studies of multiparametric renal MRI have avoided the use of gadolinium-based contrast agents (GBCA) to date due to concerns of developing nephrogenic systemic fibrosis (NSF) in CKD. However, a large meta-analysis has demonstrated that newer class II GBCA are safe even in advanced kidney disease,^26^ and recent radiology guidelines no longer necessitate informed consent before administrating class II GBCA regardless of kidney function.^27^ The use of postcontrast MRI has been of particular value in detecting myocardial fibrosis^28^ and is now routinely used in clinical practice. Specifically, areas of myocardial fibrosis are characterised by shorter T1 relaxation times following contrast administration^29^ and greater increases in 1 /T1 (R1) from precontrast to postcontrast, quantified as ∆R1, which is proportional to contrast agent concentration.^30^ Additionally, postcontrast T1 mapping has been shown to correlate with fibrosis on myocardial biopsy,^31^ making this an area with underexplored potential in renal pathology.

Here, we outline an observational study protocol designed to explore several MRI techniques including novel methods using GBCA in multiparametric kidney MRI. The Non-Invasive Magnetic resonance imaging Biomarkers to evaLuatE histology proven kidney fibrosis in Chronic Kidney Disease (NIMBLE-CKD) study aims to develop a non-invasive imaging biomarker for kidney fibrosis in individuals with CKD.

## Methods and analysis

### Study design

The NIMBLE-CKD study is an observational cohort study that aims to develop a novel non-invasive MRI biomarker to predict the percentage of kidney fibrosis quantified by histology in individuals with CKD. A control group will consist of healthy volunteers to establish normal kidney MRI parameters. This cohort will not undergo kidney biopsy due to unacceptable risk in a healthy population. An MRI model will be derived from a cohort of individuals with CKD who have undergone kidney biopsy, which will be validated against a second CKD participant cohort. CKD participants will be recruited consecutively and randomly assigned to either the derivation or validation cohorts, respectively. The study cohorts, timeline and procedures are outlined in figure 1.

**Figure 1 F1:**
[figure not shown]
NIMBLE-CKD study cohorts and timeline. CKD, chronic kidney disease; NIMBLE, Non-Invasive Magnetic resonance imaging Biomarkers to evaLuatE histology proven kidney fibrosis.

### Study population

Healthy volunteers will be identified and recruited locally. Potential CKD participants planned for kidney biopsy due to clinical indications will be identified by their treating nephrologists. The inclusion criteria for healthy volunteers include age ≥18 years, no chronic medical conditions, eGFR >90 mL/min/1.73 m^2^ and absence of haematuria or proteinuria on urinalysis. The inclusion criteria for CKD participants include age ≥18 years, eGFR >15 mL/min/1.73 m^2^ and having undergone kidney biopsy within 1 month. Exclusion criteria for all participants include a contraindication to MRI (eg, MRI incompatible implantable devices, claustrophobia), contraindication to GBCA, and pregnant or breastfeeding females. Additional exclusion criteria for CKD participants include dialysis-dependent CKD and rapidly progressive glomerulonephritis on kidney biopsy.

### Data collection

#### Baseline characteristics

Baseline characteristics of all participants including age, height, weight, serum creatinine and eGFR based on the CKDEpidemiology Collaboration (CKD-EPI) formula^32^ will be collected and recorded. Additional clinical characteristics for CKD participants will be obtained from medical records including blood pressure, haemoglobin, urinary albumin excretion (spot albumin to creatinine ratio), presence of haematuria, medical comorbidities and concomitant medications including diuretics, renin–angiotensin system inhibitors and sodium-glucose cotransporter-2 inhibitors. Baseline characteristics for each cohort will be reported and compared.

#### Kidney biopsy and pathology analysis

Percutaneous kidney biopsy will be conducted using ultrasound or computed tomography guidance based on the treating physician’s discretion. Histopathological samples of eligible participants will be reviewed prior to proceeding with MRI to ensure the exclusion criteria are not met.

All histopathological samples will be visually assessed and scored by two independent renal pathologists, who will be blinded to the MRI results. Tubulointerstitial fibrosis (TIF) will be assessed by Masson trichrome staining and quantified based on the percentage of cortex affected. The degree of TIF will be scored as a continuous variable from 0% to 100% and reported as the average of the two values from each pathologist. Based on this score, TIF will also be categorised based on the standard clinical scoring system (TIF 0 (<10%), TIF 1 (10%–25%), TIF 2 (26%–50%) or TIF 3 (>50%)). Other features of chronic kidney damage, including glomerulosclerosis, tubular atrophy and arteriosclerosis, will similarly be graded.^33^ The presence of primary renal (glomerular, tubular, interstitial and vascular) pathology and the formal histopathological diagnosis will also be recorded.

#### MRI acquisition

All MRI will be acquired using a 3.0 Tesla MRI scanner with an 18-channel body array coil and an integrated 32-channel spine coil as the receiver (Siemens Healthcare, Erlangen, Germany). Multiparametric renal MRI (figure 2) will be conducted over 45 min. Participants will be fasted for 4 hours and positioned supine with arms placed alongside the body.

**Figure 2 F2:**
[figure not shown]
Representative multiparametric MRI acquired for the NIMBLE-CKD study. Example of different MRI techniques in the NIMBLE-CKD study acquired in a chronic kidney disease participant. NIMBLE-CKD, Non-Invasive Magnetic resonance imaging Biomarkers to evaLuatE histology proven kidney fibrosis in Chronic Kidney Disease.

Localisers in the axial, coronal and sagittal planes will be obtained for renal imaging. Coronal T1-weighted volumetric interpolated breath-hold examination (VIBE) sequences using a Dixon technique will be acquired to measure kidney volume. The acquisition parameters will include: slice thickness=1.5 mm, repetition time (TR)=4.21 ms, echo times (TE)=1.34 ms (out-of-phase) and 2.57 ms (in-phase), flip angle=9°, field of view (FOV)=260×320 mm, in-plane resolution=1.25×1.25 mm^2^. Coronal T1 mapping will be performed using a modified Look-Locker inversion recovery (MOLLI) sequence with a 5 (3)3 acquisition scheme during breath-hold. The parameters will include slice thickness=8 mm, TR=401.68 ms, TE=1.04 ms, flip angle=35°, FOV=218 × 256 mm, in-plane resolution=1.48×1.48 mm^2^. Coronal T2 maps will be acquired using a T2-prepared steady-state free precession with the following parameters: slice thickness=8 mm, TR=317.95 ms, TE=1.25 ms (T2 Prep Duration 0, 35, 55 ms), flip angle=12°, FOV=154×192 mm, in-plane resolution=1.98×1.98 mm^2^. Coronal T2* maps will be acquired using a multi-echo gradient echo (GRE) sequence which will include the parameters: slice thickness=8 mm, TR=54.95 ms, TE=1.22, 2.36, 3.19, 4.30, 5.13 and 6.24 ms, flip angle=20°, FOV=156×192 mm, in-plane resolution=1.98×1.98 mm^2^. Coronal DWI will be performed using single-shot Echo Planar Imaging with Spectral Attenuated Inversion Recovery fat suppression during free breathing with b-values of 50 and 800 s/mm^2^ and the following parameters: slice thickness=8 mm, TR=3500 ms, TE=68 ms, flip angle=90°, FOV=216×268 mm, in-plane resolution=1.42×1.42 mm^2^. PC imaging will be performed in the through-plane perpendicular to the renal artery at the level of the hilum using a 2D GRE sequence with PC-velocity encoding (VENC) set at 100 cm/s. The imaging parameters will include: slice thickness=6 mm, TR=38.40 ms, TE=2.65 ms, flip angle=20°, FOV=192×265 mm, in-plane resolution=1.41×1.41 mm^2^.

Gadoteric acid, a class II macrocyclic agent, will be administered via a peripheral intravenous cannula at a dose of 0.05 mmol/kg. No unconfounded cases of NSF have been reported with gadoteric acid.^34^ Postcontrast T1 maps will be obtained at 1, 5, 10, 15 and 20 min following contrast infusion using the T1 mapping parameters outlined above. All imaging acquisition parameters are detailed in table 1.

**Table 1 T1:** MRI techniques and acquisition parameters

Imaging acquisition parameter	MRI technique						
	T1-weighted	T1 map	T2 map	T2* map	DWI	Phase contrast	Postcontrast T1 map
Sequence	VIBE	MOLLI 5 (3)3	T2-prepared SSFP	Multiecho GRE	ss-EPI	PC-VENC GRE	MOLLI 5 (3)3
Orientation	Axial and coronal	Coronal	Coronal	Coronal	Coronal	Through-plane perpen-dicular to the renal artery	Coronal
Respiratory control	Breath-hold	Breath-hold	Breath-hold	Breath-hold	Free-breathing	Breath-hold	Breath-hold
Slice thickness (mm)	1.5	8	8	8	8	6	8
Slices (number)	120	3	3	3	10	1	3
TR (ms)	4.21	401.68	317.95	54.95	3500	38.40	481.68
TE (ms)	1.34 (out of phase) 2.57 (in-phase)	1.04	1.25 T2 Prep Duration 0, 35, 55	1.22, 2.36, 3.19, 4.30, 5.13, 6.24	68	2.65	1.04
Flip angle (°)	9	35	12	20	90	20	35
FOV (mm)	260×320	218×256	154×192	156×192	216×268	192×265	218×256
In-plane resolution (mm)	1.25×1.25	1.48×1.48	1.98×1.98	1.98×1.98	1.42×1.42	1.41×1.41	1.48×1.48

DWI, diffusion-weighted imaging; FOV, field of view; GRE, gradient echo; MOLLI, modified Look-Locker inversion recovery; PC-VENC, phase-contrast velocity encoded segmented; ss-EPI, single-shot Echo Planar Imaging; SSFP, Steady-State Free Precession; TE, echo time; TR, repetition time; VIBE, volumetric interpolated breath-hold examination.

#### MRI analysis

MRI will be analysed using the image analysis software Segment (Medviso, Lund, Sweden) by two independent observers blinded to the participant’s baseline laboratory and biopsy results. The first analysis of observer 1 will be used for model derivation. Intra-observer variability will be evaluated and reported following second analysis by observer 1 of 5 healthy volunteers and 15 CKD participants (total n=20) that are randomly selected. Interobserver variability will be evaluated in those same 20 participants comparing observer 1 with observer 2. All analyses will be repeated for the left and right kidneys for each participant. Total kidney, cortical and medullary volume will be measured by manually placing regions of interest (ROIs) on each slice of the coronal T1-weighted VIBE in-phase images. Motion-corrected images will be used to measure T1, T2, T2* and postcontrast T1 values. Apparent diffusion coefficient (ADC) maps will be generated from DWI. A single ROI will be manually drawn on the T1, T2, T2*, postcontrast T1 and ADC maps in the kidney cortex and medulla, avoiding areas of heterogeneity, vascular structures, cysts, haemorrhage and artefacts. Cortical and medullary values will be reported, alongside the cortical-medullary difference and cortical-medullary ratio. Cortical and medullary contrast distribution measures will be quantified from postcontrast T1 mapping images over time. Relative concentrations of the extracellularly distributing and renally excreted GBCA will be quantified in the renal cortex, renal medulla and blood pool over time as ∆R1, where 1 /T1=R1 and ∆R1=the difference between R1 before contrast and R1 at a given time point. These relative concentrations have not previously been quantified in health or disease in this manner, and the patterns of cortical contrast distribution dynamics will be evaluated in an exploratory manner using tissue kinetic modelling approaches for potential inclusion into the multivariable model. Renal artery blood flow analysis will be performed using PC scans with static tissue background correction. A manual ROI will be placed on the renal artery across all phases of the cardiac cycle. Renal perfusion will be calculated by dividing the mean renal artery blood flow by total kidney volume.

### Outcomes

The primary outcome will be the association between a multiparametric MRI marker and TIF quantified on kidney biopsy with a minimum variance of 50% (R^2^=0.5). The model for the primary outcome will include the following MRI variables: total kidney volume, cortical T1 value, cortical T2 value, cortical T2* value, cortical ADC value, renal artery blood flow, renal perfusion and cortical contrast distribution measures.

The secondary outcomes will include the association between (1) individual MRI variables and TIF, (2) combinations of MRI variables and TIF, based on significant correlations identified in (1), (3) the multiparametric MRI marker for the primary outcome and eGFR and (4) the multiparametric MRI marker for the primary outcome and albuminuria. Exploratory outcomes will include the association between (1) the multiparametric MRI marker for the primary outcome and TIF as a categorical variable and (2) individual MRI variables and TIF as a categorical variable.

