### Sample size calculation

There will be 20 participants in the healthy volunteer cohort. To detect a minimum of 50% variance (R^2^) explained by eight MRI variables, at a 0.05 level of significance and minimum power of 0.80, a sample of 24 subjects is required. Therefore, there will be 24 participants in each of the CKD participant derivation and validation cohorts.

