### Data analysis plan

All statistical analyses will be performed using R Statistical Software (V.4.1.3; R Core Team 2022). Continuous variables will be expressed as mean and SD and compared using t-tests for normally distributed data. Skewed data will be expressed as median and IQR and compared using Mann-Whitney U tests. Data normality will be assessed visually using histograms. Categorical data will be compared using χ^2^ tests. The healthy control group will determine normal MRI reference ranges for baseline comparison. All variables (MRI, TIF, eGFR and albuminuria) will be measured and reported as continuous variables for the primary and secondary outcomes. TIF will be reported as a four-level categorical variable for the exploratory outcomes.

For the primary outcome, a multivariable linear regression model including all MRI variables will be fitted to examine the association between the multiparametric MRI marker and TIF. The model will be tested and developed in the CKD participant derivation cohort. Model performance will be assessed using a prespecified minimum variance (R^2^) threshold of 0.50 and p<0.05. Patterns of missing data will be inspected and reported. Where appropriate, multiple imputation will be used to account for missing data under the missing at random assumption, and sensitivity analyses based on complete cases will be performed. A second independent CKD participant validation cohort will be used to evaluate the accuracy and sensitivity of the model using adjusted R^2^. The multivariable linear regression model will be derived using elastic net regularisation and nested resampling cross-validation in order to minimise overfitting. The agreement performance of the model will be reported using adjusted R^2^ with 95% CIs. Similar univariable and multivariable linear regression models will be fitted to examine the association between the MRI variables and TIF, eGFR and albuminuria for the secondary outcomes. All statistical tests will be two-sided and performed at a 0.05 level of significance.

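### Secondary outcome 2 selects MRI variables by significance and tests the combination with nothing separating the two steps, so its p value and R² are not valid at face value

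*Protocol article*

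**What the plan says.** Under Outcomes, secondary outcome 1 relates individual MRI variables to TIF. Secondary outcome 2 relates TIF to "combinations of MRI variables and TIF, based on significant correlations identified in (1", the (1) being that first outcome. Membership of a combination is thus decided by significance against the same outcome.

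The Data analysis plan sets one level for everything: "All statistical tests will be two-sided and performed at a 0.05 level of significance". It describes elastic net, nested cross-validation and the validation cohort in connection with the primary model. The secondary outcomes receive univariable and multivariable regressions described only as *similar*.

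The number of variables to be screened is not fixed. The Sample size calculation speaks of a "minimum of 50% variance (R^2^) explained by eight MRI variables", and Outcomes lists those eight for the primary model. The MRI analysis section, however, produces many more: "Cortical and medullary values will be reported, alongside the cortical-medullary difference and cortical-medullary ratio". Under MRI acquisition, "Postcontrast T1 maps will be obtained at 1, 5, 10, 15 and 20 min following contrast infusion".

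On size, "there will be 24 participants in each of the CKD participant derivation and validation cohorts". The text does not say which cohort, or whether both pooled, serves the secondary outcomes.

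**The concern.** A variable that passes the screen has, by construction, a correlation with TIF in that sample that is large enough to be significant. Refitting the survivors on the same patients and testing the joint fit asks a question that the screen has largely answered. The F test assumes that the predictors were named in advance, so its p value is too small. R² is biased upwards for the same reason.

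R² is the study's main performance measure, with a primary target stated as "with a minimum variance of 50% (R^2^=0.5". A short list of variables with a flattering R² would be read directly against the primary model, although only the latter has stated protection against overfitting. Screening one variable at a time can also discard variables that matter only jointly.

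**Working it through.** **Inputs from the protocol article.** Eight variables (Outcomes, Sample size calculation); 24 patients per CKD cohort; two-sided 0.05 for screen and test; perfusion calculated as flow divided by volume (MRI analysis). **Assumed:** the mutual correlation of the MRI variables (0 to 0.7), any candidate count above eight, and an ordinary refit with an overall F test.

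**1. The plan's own figure.** With R²=0.50, f²=0.5/(1−0.5)=1. For eight predictors and N=24, the noncentrality is 24 on 8 and 15 degrees of freedom, giving power 0.801; N=23 gives 0.766. The stated 24 is reproduced. No error rate is stated for secondary outcome 2.

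**2. The screen.** With 22 degrees of freedom the critical t is 2.074, so a variable passes if |r| > 2.074/√(22+2.074²) = 0.404, that is r² > 0.163.

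**3. Why the second test adds little.** Two survivors that are uncorrelated in the sample have joint R² of at least 2×0.163=0.326. Then F = (0.326/2)/((1−0.326)/21) = 5.1, against a critical value of 3.47 on 2 and 21 degrees of freedom. Passing the screen guarantees passing the test. If the two survivors are almost collinear and only just pass, joint R² stays near 0.163 and F = (0.163/2)/(0.837/21) = 2.0, which fails. Correlation among the variables therefore weakens the effect.

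**4. How often a combination forms under no association.** For eight independent variables:
- at least one passes: 1 − 0.95⁸ = 0.337
- at least two pass: 1 − 0.95⁸ − 8×0.05×0.95⁷ = 1 − 0.663 − 0.279 = 0.057

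**5. Simulation with no association, n=24, eight variables, 10,000 runs per row.**

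| Mutual correlation | ≥1 passes | ≥2 pass | ≥2 pass and p<0.05 | p<0.05 given ≥2 | Mean R² given ≥2 |
|---|---|---|---|---|---|
| 0 | 33.11% | 5.83% | 5.72% | 98% | 0.387 |
| 0.3 | 30.83% | 7.55% | 6.88% | 91% | 0.355 |
| 0.5 | 25.64% | 8.87% | 6.05% | 68% | 0.334 |
| 0.7 | 19.35% | 8.78% | 2.95% | 34% | 0.304 |

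At correlation 0.6, separate runs put the conditional figure between 52% and 56%. Building in only the perfusion link gives 7.0% formed and 90% significant once formed. Across correlations 0 to 0.6 the median raw R² is 0.30 to 0.39. Adjusted R² is 1−(1−R²)×23/(23−k) for k variables. At R²=0.39 and k=2 this is 1−0.61×23/21=0.33; over the range it runs from about 0.2 to 0.33. The true value is 0.

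**6. Wider candidate set (assumed).** Four maps with cortex, medulla, difference and ratio give 16; ΔR1 at five times in two compartments gives 10; three volumes, flow and perfusion give 5; total 31 per kidney. A significant null combination of two or more arises in about 45%, 31% and 7% of studies at correlations 0, 0.3 and 0.6. A set of 31 built with the evident links (differences and ratios, volume parts, serial time points) gives 29%.

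**7. Pooling to n=48.** The rates barely change; mean R² for the eight-variable case falls to 0.155 to 0.219.

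**The case against.** **Frequency.** A reader might infer that the plan will often report a significant combination when nothing is associated. For the eight listed variables that is not supported. The one-in-three figure is the chance that at least one variable passes, usually giving a one-variable model, which is not a combination. Significant models of two or more occur in about 3 to 7% of studies. Rates near 80% for 31 candidates likewise count single variables and treat the 31 as independent, although many are arithmetic functions of each other. Nor does the article say that the additional measures enter the screen: it says that they will be reported. This objection stands and limits the claim.

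**The safeguards may carry over.** The word *similar* may bring elastic net and cross-validation with it, and a full protocol or analysis plan may say more. This stands only in part. The article itself states the significance screen. If that screen precedes cross-validation, the folds do not correct for it; it must be repeated inside each fold.

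**The reported measure is adjusted R², with a 0.50 threshold.** Adjustment allows for the number of variables kept, not for having chosen them, and still leaves about 0.2 to 0.33. If the threshold were applied to these models too, a null model with eight candidates would reach raw R² of 0.50 with p<0.05 in under 1% of studies. The article states that threshold for the primary model.

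**No association at all is an extreme benchmark.** The Background cites earlier correlations for T1, T2* and diffusion measures. Where some associations are real, the calculation no longer gives the false-positive rate, but selection on the same data still biases R² upwards.

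**Conclusion.** The point holds for the validity of the result, not for its frequency. As written, secondary outcome 2 yields a p value and an R² that do not mean what they appear to mean. With the eight variables and 24 patients, a null combination of two or more forms in about 6 to 9% of studies. Once formed, it is significant in about 98% of cases when the variables are independent, falling to about a third at correlation 0.7. If a wider set is screened, such results become common unless the variables are strongly correlated.

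These sizes rest on assumed correlations, an assumed refit and F test, and, for 31 candidates, an assumed list. The defect itself rests only on the stated selection rule and the absence of any separation between choosing and testing. It concerns a secondary outcome; the primary model and the sample size of 24 are not touched.

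**What to change.** In secondary outcome 2, replace the univariable significance screen by the elastic net already planned. Run it on a candidate list fixed in advance, with every selection step inside each nested cross-validation fold. Alternatively, select in the derivation cohort, freeze variables and coefficients, and test that score in the validation cohort. In simulation this second route gave false positives in 1.6% of studies with eight variables and 2.8% with 31, about 5% of the studies in which anything was selected (0.016/0.317 and 0.028/0.626). Either way, report only cross-validated or validation-cohort R² for combinations, and no p values from refitting.

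If the fixed list is simply the eight primary variables, the elastic net repeats the primary analysis; the plan should then say what secondary outcome 2 adds.

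A stricter screen alone does not repair R². Testing eight variables at 0.05/8 makes combinations rare (0.1 to 0.8% of null studies), but those that form have mean R² of 0.48 to 0.54. False discovery rate control for secondary outcome 1 is optional.

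The cost is plan wording and reuse of the primary analysis code, with no added patients or scans. Recruitment is expected to run to December 2028, so the change can precede analysis. The price is a less favourable R² and fewer nominally significant combinations.
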